**Background & Rationale**

Intibucá, Honduras lies in the middle of the internationally recognized high need area called the “Central American Dry Corridor” by the UN FAO. Poverty in this rural, remote region is ubiquitous, with lack of basic services coverage, and of difficult access. Chronic undernutrition and anemia, common symptoms of chronic nutritional deficiencies, are extremely common, especially in young children under age 5. About 1 every three children show stunting, and half of them have anemia, 13% are underweight; and 3% are wasted.

These rates are among the highest in the Western Hemisphere.

Eggs have been shown to be a cost-effective solution to fighting malnutrition in rural areas of developing countries [1, 2]. A study in Ecuador showed a significant improvement in linear growth, and nutritional status after 6 months of receiving daily eggs in the region.

However, the delivery of eggs is a challenge in the region. Shoulder to shoulder and Hombro a Hombro (non-profit organizations who have been delivering health and nutrition interventions in the area since 1998) will provide vouchers to purchase 30 eggs/month to mothers of children between 6-24 months of age in communities located in Intibucá, a department in Honduras. Our role as researchers will be to evaluate the effectiveness of this egg program. The egg program will occur regardless of our involvement.

Our specific role in this project will be to request anthropometric information in Jan-Jul of 2021 and Jan 2022 from the 6 month to 2 year-old children collected as part of the daily activities of Shoulder to Shoulder and Hombro a Hombro. In addition, we will ask mothers to participate in completing a survey that will collect sociodemographic information, morbidity, feeding practices, and food insecurity. This survey will be asked every 6 months (Baseline (Jan)- 6 month (Jul) and 13 months (Jan, 2022).

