- Significant improvement in dietary diversity in children in the egg program vs. controls
- No observed changes in breastfeeding practices in children from either group

1. **Eligibility Criteria**
   1. **Inclusion Criteria**

- Healthy children ages 6 to 24 months at the time the study begins
- No cerebral palsy, birth defect or condition that may affect their growth or development.
- Children living in Intibucá, Honduras in Camasca, Concepción, Colomoncagua, Santa Lucía, or San Marcos de Sierra
  1. **Exclusion Criteria**
- Children from families that are considering leaving the region within the next 12 months
- Known egg allergy

1. **Study Design**

This is a prospective, community-cluster study that will evaluate the effectiveness of a program that will provide 30-day egg vouchers to mothers of 6 to 24 month-old children living in rural areas of Intibucá, Honduras. The program will be delivered by a local non-profit organization (Shoulder to Shoulder - Hombro a Hombro). This research study consists of a survey that will be implemented at baseline, 6 months and 12 months. (Jan 2021-Jul 2021-Jan 2022)

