**Perform baseline assessments**

Sociodemographic, food insecurity, dietary, family structure, and morbidity survey prior to beginning the program.

Visit 1

Jan 2021

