**Endline assessment:**

Dietary, morbidity, anthropometry, food insecurity survey, adherence

Visit 3

Jan 2022

1. **Enrollment**

The AIN- C program is a community-based health promotion and prevention program that the Pan American Health Organization and World Health Organization created and was adopted to the Honduran context to bring preventative health and nutrition services to children in remote rural areas in Honduras, in the Department of Intibucá. A non-profit organization has been partnering with the government for the past decade to help deliver health into these remote areas in Honduras.

This NGO has developed a program that seeks to improve the nutritional status of young children, and will provide egg vouchers to women who mother children ages 6 to 24 months in January of 2021.

A total of 402 mothers of children will be invited to participate in the survey. An estimated half of which will be from the communities that are covered by the egg intervention and half of children that will be receiving the usual standard of care that live in other communities that will not be covered by the egg intervention.

The communities that received eggs will be matched with similar size and sociodemographic communities from neighboring municipalities to be used as “controls”.

During the government-NGO usual community-health visit, the field workers will explain the purpose of the study. They will also read the informed consent outloud, in addition to providing everyone a physical copy of the consent. In addition, during confirmation of enrollment, the mother will have the opportunity to read the consent again, and voice any questions they may have on their participation. If the mother agrees to participate, then they will proceed to sign the informed consent and medical records -PHI release forms. After these consents have been signed, then the field researchers will proceed to complete the survey. The same survey will also be completed at 6 months and at 12 months. Adherence surveys will be implemented in the communities that are receiving the egg program bimonthly.

1. **Study Procedures**

Both the intervention and control groups will receive the scheduled, standard attention provided during the community-health sessions by the Honduras health services, plus any additional activities planned by the NGO. Even if they don’t want to participate.

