We will review participant’s data entry upon completion of baseline, midline and endline assessments.

1. **Study Withdrawal/Discontinuation**

The participant can manifest their desire to withdraw from the study at any time. They will just have to notify [name], the field coordinator that they no longer wish to participate and she will immediately notify the principal investigator and remove them from the study. The participant will be able to continue receiving any activities that will be receiving without any changes to that.

1. **Statistical Considerations**

To evaluate the intervention effectiveness on growth outcomes, we will use linear mixed models for continuous variables (after transforming if variables do not exhibit a normal distribution) and generalized linear mixed models with logit link for binary outcomes. Full preanalysis plan is published here: <https://osf.io/3gx4e>.

Participant data will be analyzed following an intention-to-treat principle and all available participant data for the particular outcome at baseline,6 and 12 months will be included in analysis. Models will include fixed effects for group, time, and the group x time interaction; whereas, random effects will be used for each child (for correlation of repeated measures over time) and community (for correlation of children within community), to avoid an inflation of type I error rates in the results. All models will be adjusted by age, sex, and baseline growth outcomes. ​

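### The comparison is not randomised, yet the stated models adjust for age, sex and baseline growth and name no household covariate or matching term, so residual confounding may be attributed to the eggs

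*Protocol*

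**What the plan says.** **Allocation.** Background & Rationale says of the NGO's programme: "The egg program will occur regardless of our involvement". Study Design calls the work a prospective community-cluster evaluation. No section describes random allocation.

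**Choice of controls.** Enrollment says: "The communities that received eggs will be matched with similar size and sociodemographic communities from neighboring municipalities to be used as" controls. It does not say whether this produced pairs, sets or only broad similarity between the two groups.

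**Baseline data.** The flow diagram under Study Design lists, for the first visit, a "Sociodemographic, food insecurity, dietary, family structure, and morbidity survey prior to beginning the program".

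**Model.** Statistical Considerations states: "Models will include fixed effects for group, time, and the group x time interaction". It adds that "random effects will be used for each child (for correlation of repeated measures over time) and community (for correlation of children within community"). It closes with: "All models will be adjusted by age, sex, and baseline growth outcomes". No household variable, municipality or matched set is named. The same section points to a full preanalysis plan published elsewhere, which is not available here.

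**The concern.** Age, sex and baseline value are a natural adjustment set for a randomised trial, where allocation balances the rest in expectation. Here the programme decides which communities receive eggs, and the controls live in other municipalities. The primary objective is nevertheless a causal one: the effectiveness of the eggs on linear growth. In such a design the adjustment set is the main analytic defence of the causal reading.

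Matching communities on size and broad social features does not ensure that households are alike. If egg and control households differ in wealth, food security, diet or illness, and these factors shape growth during the follow-up year, the group-by-time contrast carries that difference as well as any effect of the eggs. The variables that would reduce the problem are planned for collection at baseline, but the stated model does not use them. If they are added only once results are known, the choice is open to the charge of selection.

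**Working it through.** **1. The protocol's own precision.** Inputs from Statistical Considerations: two-sided alpha 0.05, power 80%, 140 completers per group (independent observations), and an effective 80 per group after clustering (200/2.5).

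Formula: d = (1.960 + 0.842) × √(2/n).

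- n = 140: d = 0.335 (0.336 by t-test); the protocol states 0.34.
- n = 80: d = 0.443 (0.446 by t-test); the protocol states 0.45.

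Both figures reproduce. The standard error implied by the clustered case is √(2/80) = 0.158 SD.

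**2. A second standard error, for completers.** With 140 completers per group, 15 × 140/200 = 10.5 per community and the protocol's ICC of 0.1, the design effect is 1 + 9.5 × 0.1 = 1.95. The effective n is 140/1.95 = 71.8 and the standard error is √(2/71.8) = 0.167 SD.

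**3. What a residual bias would do to the test.** The documents give neither the household imbalance nor its association with later growth, so the bias b is assumed. With no egg effect, the two-sided rejection rate is 1 − Φ(1.960 − b/SE) + Φ(−1.960 − b/SE).

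| Assumed bias b (SD) | SE 0.158 | SE 0.167 |
| --- | --- | --- |
| 0 | 5.0% | 5.0% |
| 0.05 | 6.2% | 6.0% |
| 0.10 | 9.7% | 9.2% |
| 0.15 | 15.8% | 14.6% |

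One way to reach such values is to multiply an assumed association by an assumed imbalance: 0.3 × 0.3 SD = 0.09 SD and 0.3 × 0.5 SD = 0.15 SD. Against the stated detectable effect these are 0.09/0.45 = 20% and 0.15/0.45 = 33%.

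**4. When the bias arises.** A simulation compared change in the outcome between groups, with 13 communities of 15 children per arm, no egg effect, and a household-status score that differed between groups. It used regression of change with cluster-robust standard errors, a simplification of the planned mixed model. The gaps and associations are assumed.

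| Household-status gap | Effect of status on change | Bias, unadjusted | False positives, unadjusted | False positives, adjusted for status |
| --- | --- | --- | --- | --- |
| 0.3 | 0 | about 0 | 5.1% | 5.3% |
| 0.5 | 0 | about 0 | 6.5% | 5.4% |
| 0.3 | 0.1 | 0.03 | 6.6% | 6.0% |
| 0.3 | 0.2 | 0.06 | 10.8% | 5.0% |
| 0.5 | 0.1 | 0.05 | 8.8% | 6.3% |
| 0.5 | 0.2 | 0.10 | 17.8% | 5.4% |

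When status affects only the level of growth, comparing change removes it. When status also affects change, the comparison is biased, and adjusting for the score returns the bias to about zero.

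**The case against.** A reader might infer that confounding will be reported as an egg effect. The documents do not support that certainty. The matching narrows differences between communities by design. The group-by-time model with baseline growth removes stable differences in level, as the rows with no effect on change show. Bias needs a factor that still differs after matching and also acts on growth after baseline. Nothing in the documents shows that such a factor exists or how strong it is.

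A reader might also take the missing matched-set term as a source of confounding. It is not one by itself: omitting it mainly affects precision and the standard error. It is not even certain that identifiable sets exist.

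Finally, the protocol lists covariates without saying that no others will be used, and the preanalysis plan may add some. Detail of this kind is often left to such a plan. That is fair as far as it goes, but the protocol does not defer the choice: it states the adjustment for all models. If the plan has a wider set, the two texts differ and must be reconciled; if it does not, the gap remains.

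**Conclusion.** The point holds as a risk of residual confounding. The comparison is non-randomised, the stated adjustment covers age, sex and baseline growth, and the household data collected at baseline have no stated place in the model. Stable level differences are largely handled; differences that act on growth after baseline are not.

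The size is unknown. Under an assumed residual bias of 0.05 to 0.15 SD and a standard error of 0.158 to 0.167 SD, false positives would be about 6% to 16% where 5% is intended. These figures show how sensitive the test is; they do not estimate the bias in this study. What the preanalysis plan says is also unknown, so the statement applies to the protocol text alone.

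**What to change.** Amend Statistical Considerations as follows.

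- Keep group, time, group by time, the child and community random effects, age, sex and baseline growth.
- Add a short list of baseline covariates, fixed before outcome data are examined and drawn from the survey domains: household social status, food insecurity, family structure, baseline diet and baseline illness. The survey is not shown, so the exact items should be chosen from it.
- If identifiable pairs or sets of communities were formed, add a term for them, mainly for precision. If not, say so.
- Report the age, sex and baseline-growth model alongside, so that readers can see how far the estimate moves.
- Reconcile the text with the preanalysis plan.
- State that the estimate rests on no unmeasured confounding. Household covariates will not remove every difference between municipalities.

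The cost is a change of wording, a few degrees of freedom and a simple rule for missing covariate values. No new visits or measurements are needed.

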**Objective(s)**

- 1. **Primary Objective:**

The primary objective of this research is to evaluate the effectiveness of an egg intervention in linear growth.

- To compare the length/height for age z-scores (LAZ) in 6 – 24-month-old children whose mothers are receiving 30 egg vouchers monthly, compared with same-aged children from similar communities that will not be covered by the egg program. Both groups will continue to receive the standard of care.
  1. **Secondary Objectives:**

1. To compare the weight-for age z-scores (WAZ) and underweight (WAZ <-2) prevalence of 6-24 month-old children in an egg program, compared with same-aged children that will receive the standard of care (controls).
2. To compare the weight-for-length/height (WHZ) z-scores and wasting prevalence (WHZ <-2) of 6-24 month-old children in an egg program, compared with controls.
3. To evaluate the effectiveness of an egg intervention in rapid weight gain (zBMI upward percentile crossing of >+0.67 SD) in 6-24 month-old children in an egg program, compared with controls.
4. To evaluate the effectiveness of the egg intervention in the prevalence of reported diarrhea and respiratory infections in 6-24 month-old children from the egg program, compared with controls.
5. To evaluate the effectiveness of the egg intervention in the prevalence of sick-child consultations and hospitalizations in the health centers, of 6-24 month-old children from the egg program, compared with controls.
6. **Outcome Measures/Endpoints**
   1. Primary Outcome Measures:

- Significantly higher length for age z-scores in children that received the egg intervention vs. controls at 6 and 12 months.
  1. **Secondary Outcome Measures**

A1. A significantly lower prevalence of stunting in children who received the egg intervention vs controls at 6 and 12 months

B2. A significantly lower prevalence of underweight in children who received the egg intervention vs. controls at 6 and 12 months.

D1. A significantly lower prevalence of rapid weight gain in children that received the egg intervention vs. controls at 12 months.

E1. A significantly lower prevalence of diarrhea in children that received the egg intervention vs. controls at 12 months.

D2. A significantly lower prevalence of respiratory infections in children that received the egg intervention vs. controls at 12 months

- Significant reduction in food insecurity in children in the egg program vs. controls

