**Midline assessments:**

Dietary, morbidity, anthropometry, food insecurity survey, adherence

Visit 2

July 2021

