The field staff that works for Shoulder to Shoulder will be implementing the survey. The field staff has experience doing research programs and will receive training in ethical principles of human subject research before the study begins.

The surveys will be shared electronically with the principal investigator ([name]). These data will not contain any names, or home addresses. The field staff will transcribe the surveys to a database, however if they fall short, the co-investigator may send photos of the completed surveys via an IU secured shared drive specific for PHI, so that the Principal Investigator can assist transcribing the surveys into a spreadsheet (see survey annex). As you can see, the survey doesn’t have names, addresses, or phone numbers.

At 6 and 12 months, we will ask the participants to complete the survey. Participants receiving the egg intervention only will also complete a small adherence survey every two months.

**In-depth interviews and process evaluation**: In addition to the structured survey, we will perform in-depth interviews and a short semi-structured survey to women who are the egg farm owners, and to mothers who are receiving the intervention. A maximum of 30 women will be interviewed. These interviews will be audio recorded, but no additional information that may identify them will be collected. The objective of these interviews will be to assess the perceptions of the egg study, identify challenges, opportunities and to evaluate the impact of the egg program in other aspects such as income generation, knowledge around chicken rearing, and opportunities to improve the delivery of the intervention.

1. **Study Calendar**

|  | Screening | 6-month visit | 12-month |
| --- | --- | --- | --- |
|  | Baseline  (1 month) | Mid  (1 month) | Endline |
| **STUDY PROCEDURES** |  |  |  |
| Study socialization | x |  |  |
| Consent | x |  |  |
| Survey | x | x | x |
| In-depth interviews |  | x | x |
| Provision of Vouchers to purchase eggs (monthly) | x | x | x |
| Anthropometric measurements | x | x | x |
| Education (monthly) | x | x | x |
| Adherence surveys (monthly) | x | x | x |

1. **Reportable Events**

An adverse event would be a breach in confidentiality. If this is the case, the Principal investigator will immediately notify the IRB, and will proceed to delete any documents that have compromised the participant’s identity.

1. **Data Safety Monitoring**

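### The only adverse event defined is a breach of confidentiality; a suspected allergic reaction to egg is neither reportable nor a named outcome and could surface only unlabelled in other health data

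*Protocol*

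**What the plan says.** - **Reportable Events.** The section defines one kind of event: "An adverse event would be a breach in confidentiality". In response, the principal investigator notifies the IRB and "will proceed to delete any documents that have compromised the participant’s identity". No health event is mentioned.
- **Data Safety Monitoring.** The whole section is one sentence, committing the team to review "participant’s data entry upon completion of baseline, midline and endline assessments".
- **Eligibility Criteria.** The exclusions include "Known egg allergy". The inclusion criteria admit "Healthy children ages 6 to 24 months at the time the study begins".
- **Objectives.** Secondary objective 4 concerns "the prevalence of reported diarrhea and respiratory infections in 6-24 month-old children from the egg program, compared with controls". Secondary objective 5 compares sick-child consultations and hospitalisations between the groups.
- **Flow diagram and Statistical Data Management.** The midline and endline assessments cover "Dietary, morbidity, anthropometry, food insecurity survey, adherence". Health-centre records are collected for every child whose mother consented.
- **Study Procedures.** Only the egg group completes the adherence survey, every two months.

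**The concern.** The exclusion criterion removes only allergy that is already known. A child who enters at 6 months may have eaten little or no egg, so a first reaction could come after the vouchers begin. The protocol foresees the hazard at entry and then drops it: no later section asks about, labels, reports or compares a reaction to egg.

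This is more than a detail left for an analysis plan. What counts as a reportable event, and what is monitored for safety, belong in the protocol. Here both are stated, and stated so that a suspected reaction falls outside them.

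Two things are at stake. A reaction that field staff hear about has no defined route to the investigator or the IRB. And the evaluation could report on growth without being able to say how often children in either group had a suspected reaction to the food being promoted.

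**Working it through.** The protocol states no figure on this point, so there is nothing to reproduce. The check is to follow a suspected reaction through each place where the protocol defines, collects or compares health events.

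| Place in protocol | Could a reaction appear? | Identified as an egg reaction? |
| --- | --- | --- |
| Exclusion Criteria | Only if known at entry | Yes, but only before enrolment |
| Reportable Events | No, confidentiality breaches only | No |
| Data Safety Monitoring | No, data entry only | No |
| Morbidity part of the survey (baseline, 6 and 12 months) | Possibly; the conditions named in the objectives are diarrhoea and respiratory infection | Cannot be checked, as the survey annex is not shown |
| Health-centre records and secondary objective 5 | Yes, if the child was taken for care | No, counted with all causes |
| Outcome Measures | Diarrhoea and respiratory infection are listed; consultations and hospitalisations are not | No |
| Adherence survey | Content not described | Not stated; egg group only |
| In-depth interviews (at most 30 women) | Possibly, if a mother raises it | Not systematic |

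So there are routes by which a reaction might leave a trace, but none that is shown to identify it. Three features weaken those routes:

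- A reaction managed at home does not enter the health-centre records.
- The consultation and hospitalisation objective has no matching entry under Outcome Measures.
- The follow-up surveys are six months apart.

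**What asking would buy.** If n children are asked and none has a reaction, the one-sided upper 95% bound on risk is 1 − 0.05^(1/n), or roughly 3/n. The inputs are from Statistical Considerations: 200 enrolled per group and 140 per group expected to complete 12 months.

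- n = 200: 3/200 = 1.5% (exact 1 − 0.05^(1/200) = 1.49%).
- n = 140: 3/140 = 2.1% (exact 1 − 0.05^(1/140) = 2.12%).

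**How many children might be affected.** The documents give no reaction rate. Purely as an assumption, 0.5% to 2% would mean 0.005 × 200 = 1 to 0.02 × 200 = 4 children in the egg group. That range has no basis in the protocol, and part of any general allergy rate is already removed by the exclusion criterion.

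**The case against.** The strongest reply is that the narrow definition fits the research role. Background & Rationale says the NGO will run the egg programme whether or not the study takes place, and mothers who decline the study still receive vouchers. What the research itself adds is surveys, interviews and access to records, and the main risk of those is to confidentiality. This stands as an explanation of the wording. It does not close the gap, because the researchers' declared task is to evaluate the programme, and they enrol controls and hold the records through which harms could be compared.

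The second reply is that health data are collected anyway. This stands in part. A reader might infer that reactions would never be recorded or compared, or that the study has no harm data by group. The documents support neither. Diarrhoea, respiratory infections, consultations, hospitalisations and rapid weight gain are all to be compared between groups, and a reaction that led to care could be counted among the consultations or hospitalisations. What is missing is identification as a suspected egg reaction.

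Third, the survey annex is not shown, so a relevant question may already exist. This is a fair limit, and the fix is conditional on it. Nor does the protocol forbid field staff, who work for the NGO and meet families monthly, from passing on a reaction. It simply does not ask them to.

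**Conclusion.** The point holds in this form: the reportable-event definition is closed around confidentiality, safety monitoring covers data entry only, and a suspected allergic reaction to egg after enrolment is neither reportable nor a named outcome. From the text available, it could surface only unlabelled in the morbidity survey or in all-cause care data. This should be changed, but it does not threaten the primary growth analysis.

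The number of children affected cannot be derived from the documents. With no events, a systematic question would support an upper bound of about 1.5% (200 asked) or 2.1% (140 asked). Without such a question, whether in the plan or in the unseen annex, no such bound can be given. The bounds assume accurate caregiver reports and independent children, so clustering by community would widen them. The 140 figure covers completers only. The withdrawal section does not say that reasons are recorded, so the bound would be too favourable if children left because of a reaction.

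**What to change.** 1. **Reportable Events.** Widen the definition to cover suspected allergic reaction to egg, and death, alongside confidentiality breaches, with a stated route from field staff to the principal investigator and the IRB. Making every hospitalisation reportable goes further than needed, since hospitalisations are already to be compared under secondary objective 5.
2. **Shared surveys.** Unless the survey annex already contains one, add a single fixed question on suspected reaction to egg to the 6- and 12-month surveys. Use identical wording and recall period in both groups, and refer to eating egg from any source rather than to the vouchers. Tabulate the answers by group, with the number of children asked.
3. **Adherence survey.** If the question is also placed there, use the answers for reporting and describe them for the egg group only. Controls do not complete that survey, so including its answers in the group comparison would count events in egg-group children more often simply because they are asked more often.

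The cost is a wording change, one extra item on existing forms and a few more reports to the IRB. The change concerns recording and reporting only; care of the child stays with the health services.

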With 200 children enrolled in the intervention (egg) group and 200 in the controls, we expect 140 per group to complete all 12 months. We would then have 80% power to detect a significant difference (two-sided alpha=0.05) in outcomes at 12 months (changes from baseline) between groups if the true effect size is at least 0.34 (“med/small”) for Cohen’s d (M1-M2/SD), in a simple comparison (t-test) of means if all observations are independent. In actual analysis, all 402 children will be included in linear mixed models where partial data will be included for those who dropout which will provide higher power than the completers-only analysis. Because children’s data are clustered within community in the mixed models, power is influenced by the correlation of children’s outcomes within communities. In cluster sampling, the power/sample sizes are influenced by the design effect (DE) and interclass correlation (ICC) from correlation within cluster (DE = 1 + (m-1) x ICC, where m is sample size within cluster.) With an average of approximately 15 children per community (m), and a conservative ICC of 0.1, the DE=1+15*.1=2.5. The true sample size of 200 per group may then only be as effective as a sample size of 80 (=200/2.5), and effect sizes will need to be “medium” d=0.45 to maintain 80% power with 0.05 type I error rate, with this clustered design.

**For qualitative information**, direct content analysis to organize and examine the data will be completed by two different researchers. Categories will be identified and coded to determine consistency, frequency, and context until saturation. Information will be then synthesized and analyzed.

1. **Statistical Data Management**

The field researchers will collect data in paper surveys. The paper surveys will not be identified with the name of the participant but with a code that will be linked to a list with the names and codes of the participants and will be stored in a locked cabinet. The paper surveys will also be stored in a lock cabinet in a secured office in the headquarters of Shoulder to Shoulder/Hombro a Hombro until the study finalizes. The field staff will transcribe those surveys to an excel spreadsheet. In the case that they are falling behind, they will take photos of the survey answers. The photos will be uploaded to an IU secured shared drive in either google drive or Microsoft teams so that the IU-investigator can help digitalizing the answers into the excel spreadsheet.

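### The transformation rule checks the raw variable and does not exempt LAZ, so if it is applied the primary result leaves the z-score scale of the objective (minor)

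*Protocol*

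**What the plan says.** The Protocol's Statistical Considerations section opens its analysis plan with "To evaluate the intervention effectiveness on growth outcomes, we will use linear mixed models" for continuous variables. It adds the condition "after transforming if variables do not exhibit a normal distribution". The condition refers to the variables, not to model residuals. It covers growth outcomes as a class, with no exception for the primary one. The same section refers to a full preanalysis plan published elsewhere, which is not at hand.

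The model is then described: "Models will include fixed effects for group, time, and the group x time interaction", with random effects for child and community and adjustment for age, sex and the baseline growth outcome.

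The target of the primary analysis is on the z-score scale. The Objective(s) section states it as "To compare the length/height for age z-scores (LAZ) in 6 – 24-month-old children", and the primary outcome measure is "Significantly higher length for age z-scores in children that received the egg intervention vs. controls at 6 and 12 months".

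**The concern.** Two things in the rule do not fit the model or the objective.

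First, the check is on the wrong quantity. The pooled distribution of LAZ mixes groups, visits, ages, sexes and communities. It can look non-normal while the residuals and random effects are normal, and it can look normal when they are not.

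Second, the remedy changes what is estimated. LAZ is already a standardised score with a direct meaning. After a non-linear transformation, the group-by-time coefficient is a contrast on another scale and does not convert back to one LAZ difference. A log or square root also cannot take negative values without an added constant, and that constant affects the size of the contrast.

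At stake is whether the primary result can be read as the mean LAZ difference that the objective promises.

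**Working it through.** **1. Stated power figures (not in dispute).** Two-sample t-test, two-sided alpha 0.05, 80% power:
- 140 completers per group: detectable d = 0.336; the Protocol says 0.34.
- Effective 80 per group, taken as the Protocol gives it: detectable d = 0.446; the Protocol says 0.45.

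Both reproduce. Keeping LAZ untransformed changes neither.

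**2. Does the check look at the right thing?** A constructed, deliberately exaggerated example: 200 values from a normal distribution with mean -2.5 and SD 0.5, and 200 with mean -0.5 and SD 0.5. The two means stand for two levels of a fixed effect. A Shapiro-Wilk test on the pooled variable gives p = 4e-12. On the residuals after fitting the two means it gives p = 0.95. The model assumption holds, yet a check on the variable would call for a transformation.

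**3. Is a transformation needed for valid inference?** Simulation of a t-test on community means, 20,000 runs per setting.
- From the Protocol: 200 children per group, about 15 per community, ICC 0.1.
- Assumed: 13 communities per group (200/15 = 13.3), the skewness values, normal community effects, and one time point in place of the three-visit model.

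| Child-level errors | Type I error | 95% coverage at d = 0.45 | Power at d = 0.45 |
| --- | --- | --- | --- |
| Normal | 0.049 | 0.951 | 0.79 |
| Skewness -1 | 0.050 | 0.948 | 0.78 |
| Skewness 2 | 0.050 | 0.952 | 0.79 |

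Untransformed analysis holds its error rate, coverage and power under moderate and even strong skewness.

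**4. Would a log or root need a shift?** Background & Rationale gives about one child in three stunted. Assume that stunting means LAZ below -2, and that LAZ is normal with SD 1. Then mean LAZ = -2 + 0.43 = about -1.6, and about 94% of values are negative. Under the same assumptions, 13% underweight gives about 81% of WAZ values negative. The 3% wasted gives a mean WHZ of about -0.12 and about 55% negative, so the point is strong for LAZ, fair for WAZ and weak for WHZ.

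**5. What would a shift do?** The Protocol names no transformation, so log(LAZ + c) is an illustration only. An assumed gain of 0.3 z becomes ln((LAZ + 0.3 + c)/(LAZ + c)):

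| c | At LAZ -3 | At LAZ 0 | Ratio |
| --- | --- | --- | --- |
| 5 | ln(2.3/2) = 0.140 | ln(5.3/5) = 0.058 | 2.4 |
| 6 | ln(3.3/3) = 0.095 | ln(6.3/6) = 0.049 | 2.0 |
| 7 | ln(4.3/4) = 0.072 | ln(7.3/7) = 0.042 | 1.7 |
| 10 | ln(7.3/7) = 0.042 | ln(10.3/10) = 0.030 | 1.4 |

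The same LAZ gain has different sizes depending on the child's starting point and on the constant chosen.

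**6. The interaction.** Assume controls start at -1.2, egg children start at -1.6, and both fall by 0.4. On the z-score scale the group-by-time effect is zero. On log(LAZ + 6) it is ln(4.0/4.4) - ln(4.4/4.8) = -0.0953 + 0.0870 = -0.0083. Multiplied by the average shifted level of 4.4, that is about -0.04 z. The effect is small, but the transformation alone creates it.

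**The case against.** The strongest reply is that the harm may never occur. LAZ is a standardised score and may look close to normal. The Protocol names no test or threshold, and judging normality from plots would fit its wording. The preanalysis plan may say that residuals are checked, or may keep z-scores as they are. The phrase is also common shorthand in a short protocol. All of this stands, and it is why the point is minor. It does not make the written rule sound: it names the variable as the trigger and does not exempt the primary outcome.

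Four stronger readings are tempting, and the document does not support them.

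- **That the rule is likely to be triggered at about 400 children.** This needs a formal test and a known degree of skewness, and the Protocol gives neither. Pooling all visits to raise the count would treat repeated measures within children and communities as independent.
- **That a transformed result could not be compared with the planned effect size.** The power statement, "if the true effect size is at least 0.34", is in Cohen's d for outcomes in general. That is unitless and can be computed on any scale. The conflict is with the objective and the primary outcome measure, not with the power statement.
- **That all three z-scores are mostly negative here.** The 3% wasting figure does not support this for WHZ.
- **That the scale would be picked to suit the result.** The condition is written in advance, and a pooled normality check need not reveal the group difference.

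**Conclusion.** The point holds as a minor one. The rule checks the raw variable where the model's assumption concerns residuals and random effects. If it is applied to LAZ, it takes the primary contrast off the scale on which the objective and primary outcome are stated. There is no compensating gain in validity: untransformed, type I error stayed at 0.049 to 0.050 and coverage at 0.948 to 0.952 across the skewness values tried.

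The size of any distortion cannot be fixed from the document, because no transformation is named. The 1.4- to 2.4-fold ratios show what one family of log shifts would do, not what is planned. The conclusion rests on the rule being triggered for LAZ, on the unseen preanalysis plan not restricting it, and on a simplified simulation with 13 communities per group. No stated figure is wrong on this point.

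**What to change.** In Statistical Considerations, replace the transformation condition with wording to this effect: LAZ, WAZ and WHZ are analysed on the z-score scale without transformation; model residuals, not the raw variables, are examined; if residuals are clearly non-normal, the scale is kept and community-level robust or bootstrap standard errors are reported as a sensitivity analysis. If the preanalysis plan already says this, bring the Protocol sentence into line with it.

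The cost is one sentence and, if needed, one extra model run. It needs no new data and no change to the sample size or the power statement.
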